### Adverse events

Information on any unexpected adverse events deemed to be related to study participation will be collected and reported to the chief investigator within 24-h of its occurrence. A standardised proforma will be completed by the study site clinician which will detail the time and date of the incident, severity of the event, the relationship to the study and the following action taken and outcome. All serious adverse events will be recorded and discussed directly with the MODREC. Reporting of safety incidents will be duplicated using existing clinical health and safety reporting procedures and in accordance with the principles of good clinical practice (GCP).

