### Blinding

Given the nature of BFR, it is not possible to blind participants to their treatment allocation. The clinical staff who deliver the study interventions and collect outcome data for the main RCT must also be, by necessity, un-blinded. The following outcome measures will be assessor blinded: Decline knee bend, QASLS and all the outcome measures collected in the nested mechanistic study.

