### Statistical methods and analysis

Descriptive data will be reported as the mean and standard deviation (SD) for continuous variables and frequency statistics for non-continuous variables. Prior to statistical analysis, tests to establish the normality of data distributions will be performed and, where appropriate, variance-stabilising transformations will be applied. Analysis will be conducted on a modified intention to treat basis, including all available outcomes at course discharge regardless of compliance to treatment. All tests will be two-sided, and alpha will be set at 0.05. Assumptions for all tests will be considered and adhered to. In the primary analysis, a mixed-effects regression analysis will be used to assess the effects of the interventions on primary outcome scores at course discharge (T2) between the two treatment groups, after adjusting for fixed effects of biological sex at birth and baseline (T1) primary outcome scores, with study site centre included as a random effect. The treatment effect estimates will be presented from the adjusted mixed model with 95% confidence intervals (CI) and P-values. This mixed-effects model will be used for all secondary outcome measures. Supporting analysis of the primary outcome will include: A per-protocol analysis including patients with compliance > 80% to intervention; a repeat of the primary analysis with additional adjustments for baseline values and a mixed effects model to compare primary outcomes at three-months post intervention between the two treatment groups. In addition to the primary adjusted analysis, the unadjusted mean differences between groups will be compared using t-test for independent groups, reporting 95% CI. Sub-group analysis will be conducted by diagnostic sub-group, biological sex at birth, age and pain levels at baseline. Study participant flow will be recorded and reported in accordance with the Consolidated Standard of Reporting Trials (CONSORT) guidelines. Analysis will be conducted on a pairwise case basis. Therefore, all missing data will be reported, and patterns investigated. Sensitivity analysis will be conducted using multiple imputation techniques to assess the effect of missing data on primary outcomes. Post intervention adverse events between groups using Fisher’s exact test. All analysis will be conducted using SPSS.

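### As written, non-serious adverse events are collected only if unexpected and judged related, so the planned Fisher comparison between arms may reflect differential recording (should fix; cheap to change)

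*Protocol article*

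**What the plan says.** Four statements in the protocol article bear on this point.

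- **Adverse events, collection.** "Information on any unexpected adverse events deemed to be related to study participation will be collected and reported to the chief investigator". The sentence ends with a 24-hour limit.
- **Adverse events, serious events.** "All serious adverse events will be recorded and discussed directly with the MODREC". Neither expectedness nor relatedness is a condition here.
- **Adverse events, who completes the form.** "A standardised proforma will be completed by the study site clinician which will detail the time and date of the incident", along with severity and "the relationship to the study and the following action taken and outcome".
- **Statistical methods and analysis.** "Post intervention adverse events between groups using Fisher’s exact test". The sentence has no verb and does not define the events or the period.

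The Blinding section adds: "The clinical staff who deliver the study interventions and collect outcome data for the main RCT must also be, by necessity, un-blinded". It also lists what is protected: "The following outcome measures will be assessor blinded: Decline knee bend, QASLS and all the outcome measures collected in the nested mechanistic study". Adverse events are not on that list.

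**The concern.** A between-arm test of adverse events is interpretable only if events are found and recorded in the same way in both arms. Here two conditions stand between a non-serious event and the record. Both require judgement, and both can depend on the treatment received. The Background says that markers of exercise-induced muscle damage, including delayed soreness, are typically lower after LL-BFR than after conventional high-load training. The same soreness could thus count as expected under HL-RT and go uncollected, yet count as unexpected under LL-BFR and be collected. Conversely, a cuff-site symptom might be called a known effect of the cuff and be left out.

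Events that are never collected cannot be recovered in the analysis. The Data management section also says that no formal data monitoring committee was required, so the event records carry more of the safety evidence than they otherwise would. Tolerability is part of the case for LL-BFR, which the Discussion presents as an option for patients unable to tolerate heavy loads.

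**Working it through.** **Step 1: what the rule lets through.** The article gives no adverse event rate, so there is no figure of the plan to reproduce. Reading its sections together:

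| Non-serious event | Route into the record, as written |
|---|---|
| Unexpected and deemed related | Collected, reported within 24 hours |
| Unexpected, deemed unrelated | None stated |
| Expected, related | None stated |
| Expected, unrelated | None stated |

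Serious events are all recorded. Safety incidents are duplicated in existing health and safety reporting, which is not described as a source of trial data.

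**Step 2: who judges.** The article does not say who decides expectedness or relatedness. The site clinician completes the form, including the relationship item, and site staff are un-blinded. The natural reading is that the judgement is made with knowledge of the arm.

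**Step 3: what a differential filter does to the test.** Inputs from the article: 75 per arm, two-sided alpha 0.05, Fisher's exact test. Assumed, because the article gives none: the true proportion of participants with an event, p, and the share recorded in each arm, k1 and k2.

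The recorded proportion in arm i is p × ki. The rejection probability is the sum, over all pairs (a, b) with Fisher p ≤ 0.05, of Bin(a; 75, p × k1) × Bin(b; 75, p × k2).

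Equal true rates in both arms:

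| True rate p | k1 vs k2 | Recorded | Fisher rejects |
|---|---|---|---|
| 20% | 100% vs 100% | 20% vs 20% | 3.1% |
| 20% | 50% vs 50% | 10% vs 10% | 2.7% |
| 20% | 50% vs 30% | 10% vs 6% | 8.5% |
| 20% | 80% vs 50% | 16% vs 10% | 13.7% |
| 30% | 80% vs 50% | 24% vs 15% | 21.9% |
| 40% | 80% vs 50% | 32% vs 20% | 32.2% |
| 40% | 80% vs 30% | 32% vs 12% | 80.7% |

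Masking of a true difference of 40% vs 20%:

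- All events recorded: power 71.4%.
- 50% recorded in the first arm and 80% in the second: 0.40 × 0.50 = 20% against 0.20 × 0.80 = 16%, and power falls to 6.4%.

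**Step 4: what this shows.** With the same filter in both arms, the test keeps its level: at most 3.7% over true rates of 20% to 40%. Filtering as such does not inflate false positives, although it does discard events. Inflation or masking comes from a filter that differs by arm, and it can go either way.

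**The case against.** **It may be only an expedited-reporting rule.** Sending unexpected, related events to the chief investigator within 24 hours is the usual shape of such a rule. A relationship item on the form would also add little if every recorded event were already deemed related. This reading is possible. But the sentence governs collection as well as reporting, and no other route for non-serious events is described. If expedited reporting was the intent, the proposed change only makes it explicit.

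**A journal article condenses the full protocol.** Lists of expected events, causality procedures and collection windows are properly left to it, and their absence is not the point here. The point is a collection rule that the article does state.

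**The main symptoms are captured elsewhere.** This largely stands for the course itself. The monitoring booklet (Table 3) records knee pain and muscular discomfort on a visual analogue scale in both arms, with no expectedness or relatedness filter, and the numeric pain rating scale is collected at T1, T2 and T3. That softens the loss for those symptoms. It does not cover other events, and nothing says that it feeds the Fisher comparison.

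**Adverse events are neither a listed nor a powered outcome.** This stands. The primary outcome is the LEFS at T2, and no efficacy estimate changes.

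**The rates are assumed.** This also stands. Even a recorded 16% vs 8% (12 vs 6 of 75) gives a Fisher p of 0.21, and those rates lead to rejection in about 25% of trials.

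A reader might go further and infer that the safety comparison is shown to be biased by arm, that the clinicians' decision role is stated, or that the trial's main message depends on it. The article supports none of these. Arm-dependent labelling is plausible but undocumented, the decision role is inferred, and the stated aims are physical function and pain. Nor can one conclude that events during the course are left out of the comparison: the term post intervention is ambiguous and could mean any time after treatment starts.

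**Conclusion.** The concern holds as a should-fix item. Followed as written, the collection rule drops non-serious events that are expected or judged unrelated, and the planned Fisher test could then compare recording practice as well as harm. This rests on three readings: that the sentence governs collection, which its wording supports; that un-blinded site clinicians make the judgement, which is the natural inference; and that expectation can differ by arm, which the Background makes plausible. Direction and size cannot be determined from the article. The figures above illustrate the mechanism and do not estimate this trial's bias. The primary and secondary efficacy analyses are unaffected.

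**What to change.** **Adverse events section.**

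- Record all adverse events in both arms, whatever their expectedness or relatedness, with the same prompts.
- During the course, add one line to the daily booklet. Tie it to the once-daily wellness entry and not to each training session: LL-BFR is delivered twice daily and HL-RT three times a week, so a per-session prompt would ask one arm far more often.
- For follow-up, add one question at the existing T3 review.
- Classify expectedness and relatedness afterwards against one common definition, preferably without knowledge of the arm.
- Keep the 24-hour route for unexpected related events, and the recording of all serious events, as they are.

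**Statistical methods and analysis.** Replace the incomplete sentence with a defined comparison: the number of participants with at least one adverse event from first session to T3, by arm, using Fisher's exact test, with related events as a subset.

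**Cost.** An amendment and slightly more data entry; the booklet and the T3 appointment already exist. The change is best made early, because uncollected events cannot be reliably reconstructed. If recruitment has begun, report how events were recorded before and after the change.

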## Discussion

The use of LL-BFR in rehabilitation is increasing. Previous studies have highlighted the benefits of this approach regarding muscular strength, hypertrophy, function and pain modulation within different knee pathologies [45–49]. Other study protocols typically deliver LL-BFR 2–3 times a week over a 6–8-week duration, mirroring a traditional resistance training programme approach. However, one of the advantages of LL-BFR is providing an exercise stimulus in the absence of high mechanical stress. This enables high frequency LL-BFR to be used over short durations not deemed feasible with heavy load resistance training protocols. In healthy adult populations, high frequency (twice daily) LL-BFR has shown to be a safe and effective form of exercise intervention that can elicit favourable changes in lower limb muscle strength and muscle CSA over a 2–3 week duration [54–58]. However, the potential benefits of replicating this intensive approach in the rehabilitation setting when compared to conventional rehabilitation are still unclear. This study aims to expand on the pilot and feasibility RCT delivered in UK Defence rehabilitation in 2018 [26] into a comprehensive, fully powered, pan-UK Defence multi-centre RCT. This will help determine the effectiveness and clinical utility of this approach when utilised in an intensive rehabilitation setting.

The effects LL-BFR immediately following a course of treatment are well documented. However, less is known about the longer-term impact on an individual’s rehabilitation pathway. Therefore, this study protocol includes a follow-up assessment at three-months following intervention, this will provide some additional insight as to whether any changes in outcome seen immediately post intervention led to a meaningful lasting impact for that participant and their recovery.

To our knowledge, this is the first study to assess the effect of LL-BFR on neuromuscular performance and biomechanical adaptations in a military cohort with persistent knee pain. It will also be the first study to determine whether LL-BFR elicits an increase in agonist PCSA. The clinical implications of these findings are that LL-BFR is a rehabilitation modality that has the potential to induce positive clinical adaptations in the absence of high mechanical loads and therefore could be considered a treatment option for patients suffering significant functional deficits who are unable to tolerate heavy load RT. This study will aim to optimise rehabilitation outcomes and improve the time-and cost-effectiveness of the service delivered across UK Defence Rehabilitation and beyond. Results will provide insight and knowledge to the clinical and scientific community to not only those embedded within Defence Rehabilitation, but also those working in civilian sector organisations and professional sport in the UK and abroad.

## Data Availability

Data sharing is not applicable to this article as no datasets were generated or analysed during the current study.

## Abbreviations

ACSA: Anatomical Cross-Sectional Area
ADMR: Academic Department of Military Rehabilitation
BFR: Blood Flow Restriction
BMI: Body Mass Index
CI: Confidence Intervals
CK: Creatine Kinase
CMJ: Countermovement Jump
CONSORT: Consolidated Standard of Reporting Trials
CSA: Cross-Sectional Area
DMRC: Defence Medical Rehabilitation Centre
DMSRSG: Defence Medical Services Research Strategy Group
DOMS: Delayed Onset Muscle Soreness
DSI: Dynamic Strength Index
EIMD: Exercise Induce Muscle Damage
ERI: Exercise Rehabilitation Instructor
FAA: Functional Activity Assessment
F_L_: Fascicle Length
GCP: Good Clinical Practice
HADS: Health Anxiety Depression Scale
HHD: Hand-Held Dynamometer
HL-RT: Heavier Load Resistance Training
IMTP: Isometric Mid-Thigh Pull
IPAQ: International Physical Activity Questionnaire
KOOS: Knee Injury and Osteoarthritis Outcome Score
LEFS: Lower Extremity Functional Scale
LL-BFR: Low Load Blood Flow Restriction
LOP: Limb Occlusion Pressure
MCID: Minimum Clinically Important Difference
MOD: Ministry of Defence
MRI: Magnetic Resonance Imaging
MSKHQ: Musculoskeletal Health Questionnaire
MSKI: Musculoskeletal Injury
MTU: Muscle-Tendon Unit
MVIC: Maximum Isometric Voluntary Contraction
NPRS: Numeric Pain Rating Scale
PCSA: Physiological Cross-Sectional Area
PROM: Patient-Reported Outcome Measure
PSFS: Patient Specific Functional Scale
PTP: Personalised Tourniquet Pressure
QASLS: Qualitative Analysis of Single Leg Squat
RCT: Randomised Controlled Trial
REDCap: Research Electronic Data Collection Application
RM: Repetition Maximum
ROM: Range of Movement
RRU: Regional Rehabilitation Unit
RT: Resistance Training
SAC: Scientific Advisory Committee
SD: Standard Deviation
SEM: Sport and Exercise Medicine
sEMG: Surface Electromyography
SIRBS: Sports Injury Rehabilitation Beliefs Survey
SPIRIT: Standardised Protocol Items Recommendations for Interventions Trials
SSC: Stretch-Shortening Capabilities
TSK: Tampa Scale of Kinesiophobia
VAS: Visual analogue scale
VL: Vastus Lateralis
θp: Pennation Angle
3D: Three-Dimensional
